| Background | One in three Medicare enrollees received their insurance beneﬁts through Medicare Advantage (MA) plan.^1^ After the passage of the Medicare Modernization Act, there has been a rapid increase in MA enrollment and use of skilled nursing facilities (SNF) for post-acute rehabilitation services compared to inpatient rehabilitation facilities. Previous studies examining utilization of rehabilitation services and the quality of care have focused on Medicare fee-for-service (FFS) patients.^2^ However, there is no information about the rehabilitation quantity, quality, and outcomes of care among MA patients staying in SNF. The Office of Inspector General reported that SNFs upcode the FFS patients into higher payment RUGs categories, leading to more hours of therapy without a substantial rise in case-mix (age and diagnoses at admission were largely unchanged from 2006 to 2008).^3^ It is unknown whether this inappropriate selection of higher paying RUG therapy group in SNFs is affecting MA patients or not and how it influences the clinical outcome in these two groups. Our group has recently published a paper about rehabilitation service utilization in patients with hip fracture among Medicare FFS beneficiaries.^2^ Jung et al. reported that there is an increase in the quantity of therapy among FFS patients with hip fracture without change in case mix at SNF admission.^2^ [name] is interested in extending this research in the MA population and comparing this with traditional FFS patients. Initially, we thought of using MDS-3 assessment completed on all Medicare- or Medicaid-certified nursing home residents irrespective of their insurance status. However, after doing a comprehensive literature review, we found that hospitals receiving a disproportionate share and educational training payments and supplements submit claims for MA beneficiaries.^4^ Therefore, we decided to use inpatient claims and HEEDIS for retrieving hospital related information. |

| **Data Sources** | **Variables** | **Link** | **Years** |
| --- | --- | --- | --- |
| Medicare Provider and Analysis Review (MedPAR) | Types of Fracture, Hospital length of stay, ICU, HCC score, hospital acquired conditions, and fracture management using ICD-9 procedure codes. | <https://www.resdac.org/cms-data/files/medpar-rif> | 2010-2015  Year 2010 was used to look back |

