**Timeline**:

| **Date** | **Proposed Activities** |
| --- | --- |
| November 2016 | First meeting to discuss research question- [name], a postdoc fellow, presented his research ideas and hypothesis in our regular research meeting. |
| December 2016 | Comphrensive literature review |
| January 2017 | Presented research strategy with literature review |
| February 2017 | Data retrieval and proposal drafted |
| February 2017 | Analytical cohort created |
| March 2017 | Descriptive Analysis completed |
| March 2017 | Discuss results with clinician and coauthors |
| April 2017 | Try to develop instrumental variable but could not able to find good one |
| April 2017 | Propensity Score Matching and then decided to use IPTW |
| May 2017 | Presented final analysis after using IPTW weights and SNF fixed effects |
| May 2017 | Present the results in Annual PO advisory board meeting |
| June 2017 | Sensitivity Analysis to compare long term risk: 6 moths and 1year mortality |
| July 2017 | First draft of manuscript including all tables and figures |

| **Study Retrieval Request** | |
| --- | --- |
| Data Requested | November 14 2016 |
| Analytical Cohort Completed | February 2017 |
| Unit of Analysis | Individual level |
| Research Questions | 1. Evaluate the differences in post-acute rehabilitation services utilization (physical therapy, occupational therapy) in older patients enrolled in Medicare health maintenance organizations (HMOs) and fee-for-service (FFS) systems during a short stay in skilled nursing facilities (SNFs). 2. Compare the differences in patients centered outcome associated with amount of rehabilitation services utilization during a short stay in skilled nursing facilities (SNFs). |
| Working Hypothesis | FFS patients will be receiving more rehabilitation therapy and staying longer in the SNF, and will have better outcomes. |
| Study Sample | We will select patients with a hip fracture for this study because this is an acute condition that commonly occurs in frail older adults and majority if them receives rehabilitation care in the SNF. |

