| **Inclusion Criteria** | **Dataset: MedPAR Year:** January 2010 (lookback period for 2011) through June 2015  Patients admitted to hospital with hip fracture  MS-DRG codes: 533, 534, 535, and 536  Primary ICD-9-CM diagnostic codes: 82000, 82021, 82022, 82023, 82024, 82026, 82027, 82028, 82029, 82030, 82031, 82032, 8208, 82080, 82009, and 8080  Age ≥ 65 years  Patients from hospital with no information on disproportionate share  Length of stay less than 15 days  Discharged to only SNF  Admitted to SNF within 3 days of discharge from hospital  Merge with American community Survey  Exclude previous nursing home stay in past twelve months  Exclude previous hospitalization in past twelve months  **Dataset: MDS-3** - **Inclusion Criteria**  First-time SNF admissions from acute care hospitals identified on the basis of the presence of an MDS admission assessment tracking record  Include short term and long-term stay  Patients must have at least two assessments.  Patients must have first MDS assessment within 10 days of admission to SNF  Patients must have at least second or subsequent MDS (last) assessment within 10 days of discharge from SNF or any assessment.  Exclude Patients in coma  Exclude patients’ with any missing information on variables  Exclude patients’ with extreme therapy minutes and outliers  Exclude patients’ from Hawaii, Virgin Island, and Puerto Rico  Since 2008, the MedPAR file contains claims information on MA enrollees receiving care in disproportionate share hospitals (DSH) and Indirect Medical Education or Direct Medical Education adjustments. Therefore, our study cohort will be limited to patients discharged from these hospitals. |

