| **Primary Independent Variable** | **Physical therapy (PT) and Occupational Therapy (OT)**  OT/PT Individual Minutes Number: The data in this column indicates the total number of minutes that physical therapy was administered to the resident in the last seven days.  OT/PT Concurrent Minutes Number: The data in this column indicates the total number of minutes that physical therapy was administered to the resident concurrently with one other resident in the last seven days.  OT/PT Group Minutes Number: The data in this column indicates the total number of minutes that physical therapy was administered to the resident as part of a group of residents in the last seven days.  **Measure of Rehabilitation Therapy:** We will have an average mean number of minutes of therapy per week, on the basis of the 7-day retrospective period and all assessments from the entire SNF stay. We will sum total number of individual minutes, concurrent minutes, and group minutes for PT and OT services across all MDS assessment records during patients’ entire SNF stay. Since most stays will be less than 40 days, we will calculate minutes of therapy received in the first 40 days of SNF stays. Further, we will compute average daily minutes per day by dividing the total number of therapy minutes from the SNF length of stay up to 40 days.  **SNF Length of stay** will be defined as calendar days from admission to discharge using MDS admission and discharge records. We will follow-up to 180 days in the SNF. |

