**Abbreviation:** FFS- Fee-for-Service; MA- Medicare Advantage; SNF- Skilled Nursing Facilities; HCC- Hierarchical Condition Category; ADL- Activities of Daily Living; SD- Standard Deviation; IPTW- Inverse Probability of Treatment Weighting; FTE- Full-Time Equivalent; Total RN/LPN FTE- Total number of full-time equivalent Registered Nurse and Licensed Practical Nurse; Total PT- FTE- Total number of full-time equivalent Physical Therapist; Total OT- FTE- Total number of full-time equivalent Occupational Therapist; Total MD- FTE- Total number of Full-time Physician.

**p<0.01, *p<0.05

**Table 2**: Length of Stay and Amount of Rehabilitation Care in Medicare Fee-For-Service versus Medicare Advantage Patients

|  | **Unadjusted** | | | **Adjusted** | |
| --- | --- | --- | --- | --- | --- |
|  | FFS | MA | Differences based on linear probability model  (95% CI)  [p-value] | Differences after IPTW-Adjusted based on linear probability model  (95% CI)  [p-value] | Differences after IPTW-Adjusted SNF Fixed Effect (95% CI)  [p-value] |
| SNF Length of Stay  Mean (SD) [median] |  |  |  |  |  |
| Rehabilitation Therapy (Minutes) Mean (SD) [median] | | | | | |
| Total Physical Therapy |  |  |  |  |  |
| Total Occupational Therapy |  |  |  |  |  |
| Total Rehabilitation Therapy |  |  |  |  |  |
| Rehabilitation Therapy/Day |  |  |  |  |  |

**Note:** SNF Length of Stay: follow-up to 180 days. Total Therapy: Sum of therapy minutes (Independent + Concurrent + Group) administered to the resident up to 40 days. Total Rehabilitation Therapy: Combined Occupational therapy + Physical therapy minutes. Rehabilitation Therapy/day: Total Rehabilitation therapy divided by length of stay up to 40 days.

**Table 3:** Patients Outcomes in Medicare Fee-For-Service versus Medicare Advantage Patients before and after Inverse Probability of Treatment Weighting and SNF Fixed Effect.

|  | **Unadjusted** | | | | **Adjusted** | | |
| --- | --- | --- | --- | --- | --- | --- | --- |
|  | FFS | MA | Differences based on linear probability model  (95% CI)  [p-value] | *Odds Ratio based on logit model  (95% CI)  [p-value] | Differences after IPTW Adjusted  based on linear probability model  (95% CI)  [p-value] | *Odds Ratio based on logit model  (95% CI)  [p-value] | Differences after IPTW-Adjusted SNF Fixed Effect  [p-value] |
| Change in ADL |  |  |  |  |  |  |  |
| 30-Day Hospital Readmission % |  |  |  |  |  |  |  |
| Became Long-Stay Resident % |  |  |  |  |  |  |  |

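### The cohort excludes patients on an undefined extreme of therapy minutes, which Table 2 compares between MA and FFS as an outcome; this can bias that comparison in a direction the protocol does not determine

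*Protocol*

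**What the plan says.** The Inclusion Criteria row of the protocol, in its MDS-3 part, excludes patients "with extreme therapy minutes and outliers". It does not say which tail is meant, what the cutoff is, or whether the rule works on weekly, per-stay or daily minutes. Nor does it say whether the cutoff is pooled or set by arm, or whether only erroneous records are meant. The added reference to outliers names no variable. A neighbouring criterion drops every patient with missing data on any variable.

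The role of therapy minutes is described in two ways. The variable section files them under "Primary Independent Variable", and the Dependent Variables row does not list them. Research question 1, however, is to "Evaluate the differences in post-acute rehabilitation services utilization (physical therapy, occupational therapy) in older patients" in the two insurance systems. The working hypothesis is that "FFS patients will be receiving more rehabilitation therapy and staying longer in the SNF, and will have better outcomes". Table 2 is titled "Length of Stay and Amount of Rehabilitation Care in Medicare Fee-For-Service versus Medicare Advantage Patients" and reports differences with confidence intervals and p-values for total PT, total OT, combined therapy and therapy per day. Its note defines total therapy as "Sum of therapy minutes (Independent + Concurrent + Group) administered to the resident up to 40 days".

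**The concern.** In Table 2 plan type is the exposure and minutes are the response. A patient's minutes accrue after plan enrolment and during the SNF stay, so dropping patients because of them selects the sample on the outcome under study. The propensity score in the Original Statistical Analysis section uses baseline characteristics. Its weights balance those characteristics and cannot restore patients removed because of what happened later.

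Two things are at stake. The first is the MA-FFS difference in minutes, which answers research question 1. The second is Table 3: the rule removes the whole patient, so valid data on ADL change, readmission, long stay and community discharge go as well. The only sensitivity analysis in the Timeline concerns longer-term mortality, and no analysis in the protocol keeps the excluded patients.

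**Working it through.** **Is there a figure to reproduce?** No. The protocol gives no expected difference, no mean or SD of minutes by arm, and no share of patients excluded. The roles of the variable come from the document; every distributional input below is an assumption.

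**Step 1: outcome or exposure?** The variable section labels minutes as independent. Research question 1, the first part of the working hypothesis and all four therapy rows of Table 2 put them on the left-hand side of an MA-FFS comparison. For Table 2 the rule therefore selects on the response, whatever the label. The 40-day limit ("we will calculate minutes of therapy received in the first 40 days of SNF stays") is a measurement window applied to every patient. It is not an outlier rule and is no part of this point.

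**Step 2: quantity computed.** Ratio = (FFS mean − MA mean after exclusion) ÷ (FFS mean − MA mean in all patients). A ratio of 1.00 means no distortion. The assumed mix is 75% FFS and 25% MA.

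**Step 3: valid values, pooled cutoff, similar spread or shape in both arms** (2,000,000 draws in total).

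| Assumed distribution | Top 1% dropped | Top 5% dropped | Both 1% tails | Both 5% tails |
|---|---|---|---|---|
| Normal, shift 0.2 SD | 0.942 | 0.823 | 0.872 | 0.624 |
| Normal, shift 0.4 SD | 0.949 | 0.837 | 0.876 | 0.628 |
| Gamma, means 2200 v 1900 | 0.893 | 0.693 | 0.872 | 0.613 |

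For example, in the gamma case with the top 1% dropped, 268.3 ÷ 300.3 = 0.893.

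A separate simulation used a normal shift of 0.25 SD, a gamma with shape 3 and mean ratio 1.15, and a lognormal with sigma 0.6 and log shift 0.15. It kept 87-94% of the difference with the top 1% dropped and 67-83% with the top 5% dropped. Capping at the pooled 99th percentile instead of dropping kept 96-99%.

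Across both sets, the loss at a 1% upper cut runs from 1 − 0.949 ≈ 5% to 1 − 0.87 = 13%. At a 5% upper cut it runs from 1 − 0.837 ≈ 16% to 1 − 0.67 = 33%.

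**Step 4: other assumptions the protocol equally allows.**

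| Assumption | Result |
|---|---|
| MA has larger SD (1300 v 900), top 1% / top 5% dropped | 1.196 / 1.393 |
| Same, both 1% tails / both 5% tails dropped | 0.861 / 0.536 |
| MA has smaller SD (700 v 1000), top 1% / top 5% dropped | 0.888 / 0.586 |
| Arm-specific 1st and 99th percentile cut, equal SD | 398.52 ÷ 398.56 = 1.00 |
| Lowest 5% only dropped, equal SD | 314.8 ÷ 398.6 = 0.79 |
| Tenfold recording errors in 0.5% of FFS and 1.5% of MA | true difference 298; untrimmed 129; top 1% dropped 293 |

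**Step 5: who is removed?** In the gamma case a 1% upper cut removes 1.21% of FFS and 0.38% of MA patients. With the larger MA spread it removes 0.56% of FFS and 2.32% of MA patients. The imbalance between arms can therefore run either way.

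**The case against.** A numeric outlier rule is commonly left to an analysis plan, which may exist and is not shown. The Timeline also has the cohort built in February 2017, before the descriptive analysis in March and the final models in May. This stands in part: the missing threshold alone would not be a finding, and nothing in the protocol shows that a cutoff was tuned to the result. But the protocol itself states the exclusion as a cohort criterion, and selecting on a compared outcome is a defect at any threshold aimed at valid values.

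Trimming can also protect a mean from recording errors. That stands too, as the last row of Step 4 shows, and it is why implausible records need a rule. It does not justify removing valid extremes, or removing the patient from Table 3.

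Three stronger readings are tempting. A reader might infer that the rule shrinks the MA-FFS difference. That needs assumptions about tail, pooling, spread and validity that the document does not supply. A reader might infer that it removes mainly FFS patients; Step 5 shows that this too depends on the assumptions. A reader might also link the rule to the Background, where upcoding of FFS patients is described as "leading to more hours of therapy without a substantial rise in case-mix", and conclude that it deletes the very signal of interest. A move into higher-paying categories can shift whole groups of patients without creating statistical outliers, so that is possible but not shown.

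**Conclusion.** The point holds in a limited form. The protocol selects its cohort on an undefined extreme of a post-enrolment variable that Table 2 analyses as an outcome, and it plans no analysis with those patients kept. This can bias the MA-FFS difference in minutes. Attenuation of roughly 5-13% (1% upper cut) or 16-33% (5% upper cut) follows only for valid values, a common cutoff and similar spread in the two arms. Under other assumptions the difference grows, stays the same or moves closer to the truth. Neither direction nor size can be derived from the document.

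The loss of these patients from Table 3 is certain, but its effect there has not been quantified. The conflict between the independent-variable label and the use of minutes in Table 2 should be reconciled in the text. The change should be made: the defect in the rule is clear and the remedy is modest.

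**What to change.** 1. Replace the exclusion with one plausibility rule for minutes, written as a number, fixed without reference to plan type and identical in both arms. It sets only implausible minutes records to missing. A purely physical limit is too loose: 7 × 24 × 60 = 10,080 minutes in the seven-day window, so a tenfold error on 600 minutes (6,000) would pass.
2. Exempt these patients from the neighbouring missing-data exclusion. Otherwise setting the minutes to missing still drops the patient. They then stay in all Table 3 outcomes.
3. Make the analysis that keeps all valid values primary. Add one sensitivity analysis with minutes capped, not dropped, at the pooled 99th percentile.
4. Report the number of affected records per arm.
5. State that minutes are an outcome for research question 1 and Table 2.

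Cost: the cohort changes, so the propensity score, the weights and Tables 1-3 must be re-run. SDs in Table 2 will be somewhat larger. Some recording errors below the plausibility limit may remain in the primary analysis; the capped run limits their influence.

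### Table 2's total and per-day therapy sum 7-day look-back minutes without regard to the days covered, so they reflect assessment count and length of stay as well as therapy

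*Protocol*

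**What the plan says.** The Primary Independent Variable row of the protocol describes the basic therapy field as "minutes that physical therapy was administered to the resident in the last seven days"; the concurrent and group fields use the same seven-day span. Under Measure of Rehabilitation Therapy the protocol then does three things.

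- It names a mean number of therapy minutes per week, based on the seven-day periods.
- It builds a total: "We will sum total number of individual minutes, concurrent minutes, and group minutes for PT and OT services across all MDS assessment records", over the whole SNF stay. The next sentence restricts the span: "we will calculate minutes of therapy received in the first 40 days of SNF stays".
- It builds a daily rate by "dividing the total number of therapy minutes from the SNF length of stay up to 40 days". The Table 2 note confirms that this is a simple quotient: "Total Rehabilitation therapy divided by length of stay up to 40 days".

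Length of stay is "defined as calendar days from admission to discharge using MDS admission and discharge records". On the number of assessments, the Inclusion Criteria row says "Patients must have at least two assessments". It asks for the first within 10 days of SNF admission and a last one within 10 days of discharge, the latter loosened by an allowance for any assessment. It gives no maximum and no spacing.

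Table 2 has five rows: SNF length of stay, three totals (physical, occupational, combined) and combined therapy per day. The weekly mean has no row.

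**The concern.** A sum of seven-day look-backs is the therapy that fell inside the windows. It is not the therapy given during the stay or during its first 40 days, although the Table 2 note presents it as the latter. No step fills the days between windows, corrects for overlap, or divides by the days observed. The recorded total therefore follows the number of assessments. The recorded daily rate follows that number and, at a given number, falls as the stay lengthens.

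Therapy use is the subject of research question 1, and the working hypothesis is that FFS patients both receive more therapy and stay longer. A daily rate that depends mechanically on length of stay is a poor yardstick for that comparison. Because the protocol writes out the formula itself, and repeats it in the Table 2 note, this is not a detail left to a later analysis plan.

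**Working it through.** The protocol gives no therapy figure to reproduce, so the check works through its definition.

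**Inputs from the protocol:** a seven-day look-back per record; a numerator summed over records; a denominator D = min(LOS, 40); at least two assessments per patient.

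**Assumptions, not in the protocol:** a constant true rate of r minutes per day; the assessment days shown below; windows that hold only therapy since SNF admission; r = 60 where minutes are shown. The ratios do not depend on r.

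**Formula.** Let W be the total window-days: each window's days since admission, at most 7, added over the k records.

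- Recorded total = r × W
- Recorded per day = r × W / D
- Recorded / true = W / D, which is 7k / D when every window is full

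The measure is right only when W = D.

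**Ratios for particular patients**

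| Stay (days) | Assessment days | W | D | Recorded / true |
| --- | --- | --- | --- | --- |
| 30 | 5, 14, 30 | 5 + 7 + 7 = 19 | 30 | 0.63 |
| 30 | 8, 30 | 7 + 7 = 14 | 30 | 0.47 |
| 40 | two full windows | 7 + 7 = 14 | 40 | 0.35 |
| 10 | 5, 10 | 5 + 7 = 12 | 10 | 1.20 |

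The first two patients have the same stay and the same true therapy, yet the second is recorded 26% lower (14/19 = 0.74). In the last row, days 4 and 5 lie in both windows.

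**In minutes, with a true 60 per day and full windows**

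- Two assessments record 2 × 7 × 60 = 840 minutes. Per day that is 60 for a 14-day stay, 42 for 20 days, 30 for 28 days, and 21 for 40 days or more.
- In a 28-day stay, 2, 3, 4 and 5 assessments record totals of 840, 1260, 1680 and 2100, and 30, 45, 60 and 75 per day. The truth is 1680 and 60.

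**What this does to a comparison of groups with equal true intensity**

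- Same stay (28 days), 3 versus 2 assessments: a spurious difference of 1260 − 840 = 420 minutes in the total and 45 − 30 = 15 per day.
- Same count (3), stays of 30 versus 20 days: recorded totals are equal (1260 each), although the true totals are 1800 and 1200. The daily rates are 42 versus 63, a spurious deficit of 21 per day for the longer-stay group.
- Count in proportion to stay (3 in 30 days, 2 in 20 days): the daily rate is 42 in both, so its contrast is not biased but scaled by 0.70. The totals differ by 1260 − 840 = 420 instead of the true 600.

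**Numerator span.** If the sum runs over the whole stay while the divisor stops at 40, eight windows give 56/40 = 1.40, or 84 per day for a true 60.

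**Check of the remedy.** Summed minutes divided by W give r × W / W = r for every patient above. For the 10-day stay this is 12r/12 = r, and the total is r × 10, as it should be.

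**The case against.** The strongest reply is that error in the measure need not bias the group comparison. The protocol gives no assessment counts, schedule or spacing by group. If the count rises in proportion to the stay, both groups' daily rates shrink by the same factor. SNF fixed effects also compare patients within a facility, and so remove differences between facilities in average assessment frequency. This stands. A reader might infer that part of any MA–FFS difference must be an artefact, or that the formula favours the FFS hypothesis. The documents support neither. At a fixed count, the longer-stay group gets the lower daily rate, which would work against the hypothesis if FFS stays are longer.

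What remains is within-facility difference in coverage. The propensity model under Original Statistical Analysis lists hospital stay, but neither SNF stay nor assessment count. Neither weighting nor fixed effects therefore corrects such a difference.

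Two further replies limit the scope. The divisor is the stay capped at 40 days, not the whole stay; the protocol expects most stays to be shorter than 40 days, and for those the two coincide. The protocol also already names a weekly mean that does not grow with the number of windows. That is true, but Table 2 does not report it.

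**Conclusion.** The point holds for the measure itself. As defined, the three totals and the daily rate in Table 2 depend on assessment count, and the daily rate also on length of stay. With constant true therapy the recorded value ranges from 0.35 to 1.20 of the truth in the worked cases, given the assumed assessment days. A total should of course rise with length of stay; the fault is that this one rises with the number of records instead.

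For the MA–FFS contrast the conclusion is conditional: it may be distorted if the share of the stay covered differs between groups within facilities. Direction and size cannot be derived from the document.

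SNF length of stay comes from admission and discharge records and is unaffected. Research question 2 speaks of outcomes in relation to the amount of therapy, and a reader might infer that Table 3 is affected too. Its columns compare FFS with MA and list no therapy term, so the document does not support that.

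**What to change.** - **Intensity:** summed look-back minutes divided by total window-days, with each window cut at SNF admission. Overlapping days should count in the divisor as often as they occur in the minutes. Dividing by distinct days does not work: each field is described as one seven-day total, so overlapping minutes cannot be removed, and the 10-day example still gives 12/10 = 1.20. This measure is in essence the weekly mean already named. It differs only where admission shortens a window: on days 5 and 10 the weekly mean is 12r/2 = 6r against a true 7r.
- **Total to day 40:** intensity × min(LOS, 40), using only windows within the first 40 days. Reconcile the two stated spans for the sum, whole stay and first 40 days.
- **Table 2:** report these two measures. Add assessments per patient and share of the stay covered, by group, so that readers can judge whether coverage differs. Keep the simple sum as a secondary line.

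The cost is the re-derivation of one variable from MDS data already held. The downside is that the new total assumes that therapy on uncovered days resembles therapy on covered days, which should be stated in the table note.

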| **Dependent Variables** | **Function:** Functional status will be measured using seven ADL items into a 28-point scale with 0 indicating independence and 28 indicating total dependence. Change in functional status will be computed by subtracting admission from discharge scores; negative scores will be reversed to be positive to improve understanding. The more positive score the greater the improvement.  **Hospital Readmission (yes/no):** We will use all-cause readmission to the hospital within 30 days following discharge from the index hospitalization. Because MA enrollees may be readmitted to a non-DSH hospital which may not submit claims to Medicare, so we will merge the MedPAR and HEDIS files to estimate the 30-day hospital readmission for MA enrollees.  **Long-stay resident (yes/no):** SNF patient will become a long-stay nursing home resident, if they will stay in a nursing home more than 100 days.  **Successful Discharge to the community (yes/no):** Successful discharge from SNF will be defined as being discharged to the community within 100 days of SNF admission and remaining alive in the community without being institutionalized in any acute and post-acute settings for at least 30 days. We will link MDS with MedPAR and HEDIS files to estimate the Successful discharge to the community. |

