| Successful Discharge to Community % |  |  |  |  |  |  |  |

**Notes:** Change in ADL: (Discharge ADL - Admission ADL) and the score was reversed in positive for better understanding. Higher score in ADL change indicates greater improvement in functional status. Long Stay Resident: Stayed more than 100 days. Successful

Discharge to the Community: Discharge to community within 100 days in SNF followed by uninterrupted 30 days stay in Community/home/home health.

*Odds Ratio based on logit model (95% CI) [p-value] was added after reviewer feedback

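### Read literally, the ADL-change rule gives the absolute change, so decline would score as improvement; the protocol never says that decliners keep negative values.

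*Protocol*

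**What the plan says.** The outcome is defined in the protocol's Dependent Variables row, under Function, in four steps.

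- **Scale:** seven ADL items are combined into a "28-point scale with 0 indicating independence and 28 indicating total dependence". Higher is worse.
- **Raw change:** "Change in functional status will be computed by subtracting admission from discharge scores", that is, discharge minus admission.
- **Reversal:** "negative scores will be reversed to be positive to improve understanding".
- **Interpretation:** "The more positive score the greater the improvement".

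The outcome is described again in the notes under Table 3 (Recommended Tables): "Change in ADL: (Discharge ADL - Admission ADL) and the score was reversed in positive for better understanding". The note then adds: "Higher score in ADL change indicates greater improvement in functional status".

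Neither place states what value a patient who worsens should receive.

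**The concern.** On a scale where higher is worse, discharge minus admission is negative for a patient who improves and positive for one who declines. The reversal in the Function definition is applied to negative scores. Positive scores, which belong to the decliners, are not mentioned. A programmer who follows the sentence as written flips the improvers and leaves the decliners alone, so every patient whose score changes ends up with a positive value.

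The interpretation sentence is then false for every decliner: the larger the loss of function, the larger the recorded improvement.

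Change in ADL is the first row of Table 3 and the only outcome there that is not binary. It bears directly on the working hypothesis that FFS patients will do better. Neither the propensity weighting nor the SNF fixed effects can repair an outcome that carries the wrong sign for some patients. The protocol also points other researchers to the data sources so that they can replicate the results, and they would have to work from this wording.

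**Working it through.** The protocol gives no mean, SD or proportion declining for ADL change, so there is no stated figure to reproduce. The check has two parts: the logic of the rule, which needs no assumptions, and an illustration of size, which does.

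**1. The rule applied to the scale**

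Let c = discharge − admission, with each score an integer from 0 to 28.

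- Literal rule: y = −c if c < 0, otherwise y = c. This is |c|.
- Full sign reversal: y = −c, which is admission − discharge.

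| Admission → discharge | c | Literal rule | Full reversal |
|---|---|---|---|
| 18 → 12 (improves by 6) | −6 | +6 | +6 |
| 18 → 18 (no change) | 0 | 0 | 0 |
| 12 → 18 (declines by 6) | +6 | +6 | −6 |

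There are 29 × 29 = 841 possible admission/discharge pairs. The literal rule equals |c| in all of them. It differs from full reversal in 29 × 28 / 2 = 406 pairs, and these are exactly the pairs with decline. Full reversal agrees with the stated interpretation in all 841.

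**2. The two descriptions side by side**

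| | Function definition | Table 3 note |
|---|---|---|
| Raw change | discharge − admission | discharge − admission |
| What is reversed | negative scores | the score, without restriction |
| Meaning of a higher value | more improvement | more improvement |
| Value for a decliner | not stated | not stated |

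**3. Size if coded literally (assumed values)**

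Assume that true improvement X is normal with mean μ and SD σ. Then

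- P(decline) = Φ(−μ/σ)
- E|X| = σ√(2/π) · exp(−μ²/(2σ²)) + μ[1 − 2Φ(−μ/σ)]

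Equal SDs, σ = 5:

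- μ = 4: P(decline) = Φ(−0.8) = 0.212; E|X| = 2.897 + 2.305 = 5.20, against a true mean of 4.
- μ = 3.5: P(decline) = Φ(−0.7) = 0.242; E|X| = 3.123 + 1.806 = 4.93.
- The true difference is 0.50. The coded difference is 5.202 − 4.929 = 0.27.
- Lower means, 3 and 2.5: 4.687 − 4.478 = 0.21 in place of 0.50.

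Range over the assumed SD for a true 1-point difference (means 4 and 3, equal SDs): the coded difference is 0.75, 0.52 or 0.38 for an SD of 3, 5 or 7. For a small change in the mean at fixed SD, the shrinkage factor is 1 − 2 × P(decline).

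Unequal SDs, true difference still 0.50 in favour of the first arm:

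- Mean 4, SD 5 against mean 3.5, SD 7: 5.20 − 6.27 = −1.07. The order reverses.
- Mean 4, SD 7 against mean 3.5, SD 5: 6.47 − 4.93 = +1.54. The difference grows.

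**The case against.** The strongest reply is that the sentence is loose wording for an ordinary change of sign. Discharge minus admission makes improvement negative, and the authors turn the sign round so that improvement reads as positive. The stated purpose, easier understanding, fits a change of presentation better than a new non-negative outcome. The protocol never says that reversal is confined to negative scores, never says that positive scores stay as they are, and never mentions an absolute value. The interpretation sentence holds for every patient only under full reversal. The Table 3 note supports that reading: it says "and the score was reversed in positive for better understanding", and what is reversed there is the score as a whole. The note is also in the past tense, so it may describe what was done.

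Most of this stands. A reader might infer that the study analysed the absolute change, or that the authors meant to. The documents do not support that: both interpretation sentences point the other way, and the Table 3 note does not repeat the restriction to negative scores.

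The objection does not make the rule sound. A sentence that defines an outcome should give the right value when followed, and this one does not do so for decliners. The Table 3 note helps but does not settle the matter, because reversing a score into the positive can still be read as making every value positive.

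The objection is also right about size. The figures above rest on assumed means, SDs and normality, and attenuation follows only when the SDs are equal and mean improvement is positive.

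**Conclusion.** The point holds as a defect of wording in an outcome definition. Taken literally, the Function rule yields the absolute change, contradicts its own interpretation sentence, and differs from the Table 3 note. Neither place says that decliners keep negative values. This part follows from the text and the scale alone.

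The consequence is conditional on literal coding. Decline would then count as improvement, and mean improvement would be overstated in any arm that contains decliners. The effect on the MA–FFS comparison cannot be fixed from the protocol. Under the assumed normal scores with equal SDs (means 4 and 3.5, SD 5), 0.5 becomes about 0.27; with unequal SDs the difference can shrink, grow or reverse. It would therefore be too strong to say that the comparison is biased towards no difference, or that any result is wrong. If the variable was coded as a full sign reversal, the analysis is unaffected and only the text needs correcting.

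**What to change.** Use one definition, in the same words, in the Function entry and in the Table 3 note: *Improvement = admission ADL minus discharge ADL for every patient, sign retained; negative values are decline.* Delete the sentence about reversing negative scores and its counterpart in the note. Both interpretation sentences can then stay as they are.

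Then check that the derived variable contains negative values. If it has none although some patients had a higher ADL score at discharge than at admission, the absolute change was coded, and the ADL row of Table 3 must be rerun.

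The cost is one sentence in two places and a check of one derived variable; a rerun is needed only if the check fails.
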